## Discussion

Diabetes has become one of the leading public health issues in the world and its prevention is a major objective of the World Health Organization (WHO) [2]. Prediabetes is a risk factor for type 2 diabetes. There is therefore a necessity for safe and cost-effective agents that can improve insulin sensitivity and beta-cell function in high-risk individuals [13].

On the other hand, vitamin D deficiency has become a common problem globally. Almost one billion people worldwide are estimated to live with vitamin D deficiency [45].

Low vitamin D levels are associated with higher fasting glucose [18, 46]. This association is found in both cross-sectional studies and prospective population studies [47–49].

Although conflicts in the results of previous supplementation studies are seen [4], there are several mechanisms that vitamin D might alter glucose metabolism. Vitamin D has anti-inflammatory and immune modulatory effects [50] and may also stimulate insulin release by pancreatic b-cells [51, 52].

There is a hypothesis that omega-3 supplementation may improve glycemic control, although the its mechanisms are not clear yet [53]. During a study on animal models, the following potential mechanisms were found: hepatic insulin sensitivity improvement [54] by hepatic fatty acid oxidation and reducing lipogenesis [55, 56]; increased production of adipocytokines (e.g. adiponectin and leptin) [57]; direct [58] and indirect [55] anti-inflammatory effects and associated improvements in insulin sensitivity in the liver, muscle, and adipose tissue; and modulation of incretin hormones, which are involved in glucose-stimulated insulin secretion [59].

Lack of n-3 PUFA effects on insulin sensitivity has been found in a meta-analysis [60], while association of short-term fish oil supplementation with increasing insulin sensitivity has been shown in another meta-analysis among people with metabolic disorders [61]. However, two studies have shown improved glycemic status in patients with new onset type 1 diabetes mellitus and women with GDM with combined high-dose omega-3 and high-dose vitamin D therapy [22, 23]. Considering the results of the two studies mentioned above, the combination of vitamin D and omega-3 might provide either synergistic or complementary effects in prediabetes, which will be evaluated through this 2 × 2 factorial study design. Vitamin D interfering with omega-3 was not reported in previous studies.

This is the first randomized controlled trial that will determine the effect of vitamin D and omega-3 on glycemic status, serum lipids, and psychological distress in women of reproductive age with prediabetes and hypovitaminosis D. This trial, therefore, investigates potential effects of these two supplements in decreasing the risk factors of type 2 diabetes.

### Strengths and limitation of study design

The strengths of this study are its factorial design to assess the individual, complementary or synergistic effects of both interventions, and triple blinding of the participants, investigators, and statistical analyzer to reduce bias.

The advice to participants is to maintain a steady pattern of diet and physical activity. Reducing the impact of confounding factors, two questionnaires evaluate their patterns.

To assess compliance with the intervention, a capsule log and a capsule count are used.

In previous studies, toxic or adverse effect at this dose of vitamin D and omega-3 have not been reported. In this study, all of the risk factors are not evaluated so the results may not be enough to reduce the risk of diabetes completely.

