Moreover, the results of several studies show an association of vitamin D deficiency with insulin resistance, impaired insulin secretion, and their important metabolic consequences [17–19]. In addition, a meta-analysis has declared that depression is associated with a lower level of vitamin D [20]. Further, effectiveness of omega-3 on depression has been shown in another meta-analysis [21].

In some studies, it could be seen that combined high-dose omega-3 fatty acids and high-dose vitamin D therapy improved glycemic indices in patients with new onset type 1 diabetes mellitus and women with gestational diabetes (GDM) [22, 23]. Since the effect of co-supplementation of vitamin D and omega-3 on fasting blood sugar and other cardiometabolic risk factors are not well documented, this study has been designed to evaluate the complementary or synergistic effects of vitamin D and omega-3 on fasting blood sugar and other glycemic indices, serum lipids, and psychological distress in reproductive-aged women with prediabetes and hypovitaminosis D.

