## Methods/design

### Study design

This is an eight-week 2 × 2 factorial, triple-blinded (study investigators, participants, and statistical analyzer), randomized, placebo-controlled trial. Overall, 168 women of reproductive age diagnosed with prediabetes (fasting glucose 100–125 mg/mL) will be screened for enrolment in the study. This study will be conducted at Shahid Rastravesh Health Center Laboratory, Alborz University of Medical Sciences, Karaj, Iran.

Eligible participants who meet the inclusion and exclusion criteria will be randomly divided into four groups to receive double placebo (omega-3 and vitamin D placebos), omega-3 placebo and vitamin D supplement, omega-3 supplement and vitamin D placebo, and supplements of omega-3 and vitamin D.

In this factorial 2 × 2 design, we want to address five questions:
Compared to placebo, is omega-3 effective?Compared to placebo, is vitamin D effective?Are vitamin D + omega-3 more effective than placebo?Are vitamin D + omega-3 more effective than vitamin D alone?Are vitamin D + omega-3 more effective than omega-3 alone [24]?

Participants will visit the trial sites three times: at baseline (0 weeks); after three days; and post intervention (eight weeks after intervention). The flow chart of the study protocol is presented in Fig. 1.

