
### Statistical analysis

The effect of the intervention on all participants will be assessed based on intention-to-treat and per-protocol analyses. The data will be checked for plausibility by randomly checking the accuracy and completeness and source data verification. The normality of continuous variables will be determined using a Kolmogorov–Smirnov test. Appropriate statistical transformation (logarithmic transformation, square root transformation, cube root transformation, or reciprocal transformation) will be used for continuous variables with not normal distribution.

Hence, statistical analysis for continuous variables with normal distribution (parametric tests) will be used in this study.

Continuous variables with normal distribution and transformed variables will be expressed as mean ± SD. Categorical data will be presented as frequency (percentage).

To compare the mean differences within each group, before and after intervention, the paired t-test will be used for continuous variables.

For continuous variables, one-way analysis of variance (ANOVA) will be used to detect differences in sociodemographic characteristics, metabolic profiles, physical activity levels, and dietary intakes at the study baseline between the four groups.

Categorical data at the study baseline will be analyzed using the Chi-squared test between the intervention groups.

Repeated measures analysis of variance (RM ANOVA) with Bonferroni procedure to adjust for the five comparisons will be used to assess time effects and time-by-treatment (vitamin D and/or omega-3) interaction effects on all outcome variables between groups.

Since we have multiple endpoints and we will compare five pairwise comparison, all *p* values will be corrected using the Bonferroni adjustment method.

Two-way RM ANOVA with Bonferroni adjustment for comparisons will be used to assess the relationship between changes in mean serum vitamin D level and each of fasting blood sugar and other outcome variables between groups.

Levenes test for independent data in one-way ANOVA and Mauchly’s test in RM ANOVA will be used to test homoscedasticity.

All statistical measurements will be reported with 95% confidence intervals (CI). A *p* value < 0.05 will be considered statistically significant. All statistical analyses will be performed using SPSS version 24.

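### Synergy is a stated aim, but no vitamin D × omega-3 contrast is clearly specified, and the five planned comparisons do not by themselves separate synergy from additivity

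*Protocol article*

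**What the plan says.** The protocol article states the synergy aim in three places.

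- Background: "this study has been designed to evaluate the complementary or synergistic effects of vitamin D and omega-3 on fasting blood sugar".
- Discussion: the combination "might provide either synergistic or complementary effects in prediabetes, which will be evaluated through this 2 × 2 factorial study design".
- The section on strengths and limitation, near the end: "The strengths of this study are its factorial design to assess the individual, complementary or synergistic effects of both interventions".

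Study design then fixes five questions. Three are against placebo: "Compared to placebo, is omega-3 effective?Compared to placebo, is vitamin D effective?Are vitamin D + omega-3 more effective than placebo". Two are against a single supplement: "Are vitamin D + omega-3 more effective than vitamin D alone?Are vitamin D + omega-3 more effective than omega-3 alone". Sample size sets 38 per group on the basis of five pairwise comparisons. Statistical analysis adjusts for the same five: "Repeated measures analysis of variance (RM ANOVA) with Bonferroni procedure to adjust for the five comparisons will be used to assess time effects".

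The only interaction mentioned is in that repeated measures ANOVA, which "will be used to assess time effects and time-by-treatment (vitamin D and/or omega-3) interaction effects on all outcome variables between groups". A two-way repeated measures ANOVA is also planned, but it is assigned to the relation between change in serum vitamin D and the outcomes, not to the two supplements as factors. The Objectives and the primary and secondary outcomes do not mention synergy.

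**The concern.** Synergy means that the combination does more than the two single effects added together. With four arms that is one contrast:

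(combination − vitamin D) − (omega-3 − placebo).

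Zero is additivity. For an outcome to be lowered, such as FBS, a value below zero is synergy. None of the five questions is this contrast. Each compares two arms, and success on the three that involve the combination is compatible with synergy, with exact additivity and even with mild antagonism.

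At stake is one of the article's stated purposes. Without a named contrast, the trial has no pre-specified result on which a synergy statement could rest, and an interaction test chosen after the data are seen would not be pre-specified.

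**Working it through.** **Inputs.** From Sample size: FBS 86.8 (SD 6.40) with the combination and 94.6 (SD 10.30) with placebo; alpha 5%, power 80%; 38 per group after adjustment; 168 in total. No FBS unit is printed there, so FBS units are used below. The difference is 94.6 − 86.8 = 7.8. The pooled SD is √[(6.40² + 10.30²)/2] = √(147.05/2) = 8.57. Bonferroni for five comparisons gives 0.05/5 = 0.01 each.

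**The plan's own figure.** n = (1.960 + 0.842)² × 147.05 / 7.8² = 18.97, so 19, or 20 with the t distribution. The stated 20 is reproduced. The same formula at alpha 0.01 gives 28.2, so 29 (30 with t); the stated 38 does not follow from it. I take 38 as given. The total follows: 4 × 38 × 1.1 = 167.2, so 168.

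**Precision at 38 per arm, without baseline adjustment.**

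- Pairwise difference: SE = 8.57 × √(2/38) = 1.97.
- Interaction contrast: SE = 2 × 8.57/√38 = 2.78; 95% CI half-width 1.96 × 2.78 = 5.5.
- Power for the interaction at two-sided alpha 0.05: for 7.8, 7.8/2.78 − 1.96 = 0.84, giving 80%; for 3.9, 3.9/2.78 − 1.96 = −0.56, giving 29%. An interaction of 3.9 would need 152 per arm for 80% power.
- If all 42 per arm are analysed, the SE is 2.65.

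**What the five comparisons show when the interaction is exactly zero.** Simulated four-arm trials, 38 per arm, SD 8.57, two-sided alpha 0.01 per comparison. The single-supplement effects are assumptions, because the article gives only the combination's difference from placebo.

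| Assumed effect of each supplement | Combination effect | Combination beats placebo and both singles | Combination beats placebo, neither single does |
|---|---|---|---|
| 3.9 | 7.8 (the plan's difference) | 13–14% | 51% |
| 5.2 | 10.4 | 36% | 30% |
| 7.8 | 15.6 | 85–86% | 2% |

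In each row a one-contrast interaction test at two-sided alpha 0.05 would point to synergy in 2.5% of trials.

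**Why the wins do not diagnose synergy.** With 7.8 from each supplement and no interaction, the combination beats both singles in 86% of trials. With no effect of either supplement alone and an interaction of 7.8, it also does so in 86%. The pattern in the last column occurs in 51% of trials under additivity at 3.9 each, and in 91% under that pure interaction, so it is not diagnostic either.

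**Effect of baseline adjustment.** The outcome is change from baseline, and the article gives no correlation ρ between visits. Assuming equal SDs at both visits, the SE of 2.78 is multiplied by √[2(1 − ρ)] for change scores and by √(1 − ρ²) for baseline-adjusted week-8 values. For assumed ρ of 0.3, 0.5 and 0.7, this gives 3.29, 2.78 and 2.15 (change) and 2.65, 2.41 and 1.99 (adjusted). The half-width then lies between about 3.9 and 6.5.

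**The case against.** The strongest reply is that the parenthesis in the time-by-treatment sentence can be read as a model with vitamin D and omega-3 as separate factors, which would contain the needed term. That reading is possible, so one cannot say that the interaction will certainly go untested. But the sentence names no product term, speaks of effects between groups, and is tied to the five comparisons. It is ambiguous on a stated aim. A full analysis plan might settle it; the article, however, itself fixes the questions, the sizing basis and the multiplicity family, and none of these includes the contrast.

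Four stronger inferences are tempting and should not be drawn.

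- That the investigators will report wins over each single supplement as synergy. Nothing in the article says so. Benefit beyond each single agent, a fair meaning of complementary, is what the last two questions address.
- That analysing four separate arms is itself an error because it forgoes the precision of pooled main effects. Simple effects are a legitimate choice, especially when an interaction is thought plausible.
- That the 85% figure measures the risk. It needs 7.8 from each supplement, whereas the article assumes 7.8 for the whole combination.
- That 38 per arm shows an interaction test was planned, because 2 × 18.97 = 37.9 is the size for an interaction of 7.8. The article attributes 38 to the five pairwise comparisons.

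It is also fair that the five questions remain answerable with multiplicity control, and that the contrast can be estimated from the same four arms.

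**Conclusion.** The point holds as a mismatch within the article: synergy is named three times as something the design will evaluate, while the comparisons it fixes are all two-arm and no supplement-by-supplement contrast is clearly specified. The primary pairwise comparisons are not invalidated.

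The 13–14% and 51% figures illustrate how often additivity alone gives results that resemble synergy. They rest on an assumed equal split of the 7.8 between the supplements, the Sample size SDs, 38 per arm and normal outcomes. Even once specified, the interaction would be weakly estimated: without baseline adjustment, 80% power is reached only for an interaction as large as the entire assumed combination effect.

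**What to change.** Keep the five pairwise comparisons, but take them from one factorial model with terms for vitamin D, omega-3 and vitamin D × omega-3. Model either change in FBS, or week-8 FBS adjusted for baseline FBS and the vitamin D stratum used in randomization. Then state that:

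- the interaction estimate with its 95% CI is the only basis for any statement on synergy;
- it is secondary and lies outside the five-comparison Bonferroni family;
- its precision is low (SE about 2.8 and half-width about 5.5 from the Sample size SDs without baseline adjustment), so an interval that includes zero does not show additivity;
- it is judged on a named scale, since the plan allows transformations and additivity on one scale need not hold on another.

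Pooled main effects may be reported as well, but this is optional.

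The alternative is to remove the synergy wording from the Background, the Discussion and the strengths section, and to claim only the five comparisons.

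Either route costs a few sentences; the first adds one model term. Neither needs more participants or measurements. The downside of the first is a wide interval that must be reported as such. As the analyst sees only package letters, the model should be written in advance against placeholder factor codes.

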### Objectives

Compare the mean serum lipid (triglycerides [TG], total cholesterol [TC], low-density lipoprotein cholesterol [LDL-C], high-density lipoprotein cholesterol [HDL-C]) and glucose indices (fasting blood sugar [FBS], fasting blood insulin [FBI], homeostasis model assessment - insulin resistance [HOMA-IR], homeostasis model assessment - beta cell function [HOMA-B]) between the four groups and within each group, before and after intervention.Compare the means of anthropometric indices (weight, waist circumference, body mass index [BMI]) and systolic and diastolic blood pressures between the four groups and within each group, before and after the intervention.Compare the mean scores of the Depression Anxiety Stress Scale (DASS-21) and Pittsburgh Sleep Quality Index (PSQI) between the four groups and within each group, before and after intervention.Determine the relationship between changes in mean level of serum vitamin D and each of the glucose indices, serum lipids, and the mean scores of the DASS-21 and PSQI between the four groups and within each group, during intervention.

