### Study participants

Women of reproductive age with prediabetes from Karaj health centers diagnosed with FBS test (fasting glucose 100–125 mg/mL) [1, 25] will be invited to this study.

The study investigator will call participants by phone and will screen them according to the inclusion and exclusion criteria.

Eligible participants will be referred to the Shahid Rastravesh Health Center. First, the goals, methods, and benefits of the intervention will be explained by the investigator and the informed consent form will be signed by participants. At the beginning, 10 mL of blood will be taken from a peripheral vein after a 12-h overnight fast to assess plasma glucose levels, insulin, TG, HDL-C, TC, and vitamin D. After centrifuging for 10 min (3000 rpm), the serum samples will be frozen simultaneously and stored at − 80 °C until analyzed [12]. LDL-C will be estimated based on the Friedewald equation [27]. Participants will receive a three-day food record. The investigator will explain how to complete the form to each participant.

After three days, women who have been confirmed as having prediabetes (fasting glucose 100–125 mg/mL) and hypovitaminosis D (vitamin D < 32 ng/mL) [26] will be invited to the Shahid Rastravesh Health Center.

The sociodemographic characteristics questionnaire, short-form International Physical Activity Questionnaire (IPAQ), DASS-21, and PSQI will be completed with interviews. The investigator will review completed three-day food record in presence of each participant.

Anthropometry including weight, height, and waist circumference will be measured using a digital scale, stadiometer, and non-elastic tape, respectively.

Blood pressure (systolic and diastolic) will also be measured with a digital manometer.

All the above-mentioned stages, including blood sampling, completing four questionnaires (three-day food record, IPAQ, DASS-21, and PSQI), anthropometric measurements and measuring blood pressure, will be repeated after eight weeks.

At the end, the evaluated outcomes will be presented to participants privately. A Data Monitoring Committee (DMC) will also monitor during and at the end of this study (Fig. 2).

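### Diet and activity questionnaires are credited with reducing confounding, but the stated model for the non-randomised vitamin D association (fourth objective) contains neither (minor)

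*Protocol article*

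**What the plan says.** The section Strengths and limitation of study design first says "The advice to participants is to maintain a steady pattern of diet and physical activity" and then: "Reducing the impact of confounding factors, two questionnaires evaluate their patterns". The two instruments are the three-day food record and the short-form International Physical Activity Questionnaire (IPAQ). Under Study participants, both belong to the set repeated at the end: "completing four questionnaires (three-day food record, IPAQ, DASS-21, and PSQI), anthropometric measurements and measuring blood pressure, will be repeated after eight weeks".

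The Statistical analysis section names diet and activity once, in a one-way ANOVA of "physical activity levels, and dietary intakes at the study baseline between the four groups". Its other relevant lines are:

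- A paired t-test, not limited to outcomes: "To compare the mean differences within each group, before and after intervention, the paired t-test will be used for continuous variables".
- The main repeated measures ANOVA, which "will be used to assess time effects and time-by-treatment (vitamin D and/or omega-3) interaction effects on all outcome variables between groups".
- A two-way repeated measures ANOVA, which "will be used to assess the relationship between changes in mean serum vitamin D level and each of fasting blood sugar and other outcome variables".

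The last of these serves the fourth item under Objectives, "Determine the relationship between changes in mean level of serum vitamin D and each of the glucose indices", which goes on to lipids, DASS-21 and PSQI and asks for the relationship both between and within groups.

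**The concern.** A questionnaire reduces confounding only if its data enter a design decision or an analysis. Here the one named use is a test at baseline, where randomisation already makes any difference between arms a chance difference. That test controls nothing.

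The association in the fourth objective is different. Within an arm, how much a woman's vitamin D level changes is not randomised. A woman who becomes more active or changes her diet over the eight weeks may change both her vitamin D level and her glucose, lipids, mood or sleep. The analysis as stated could then credit vitamin D with an association that lifestyle produced, although the trial holds the data to examine this. The plan also asks women to keep their usual diet and activity, but names no between-arm comparison of whether they did.

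**Working it through.** No figure in the protocol bears on this point, so the check is mainly a comparison of its sections.

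**Step 1. Trace diet and activity through the article.**

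| Place | What it does with diet and activity |
|---|---|
| Strengths and limitation | Credits the two questionnaires with reducing confounding |
| Study participants | Collects both at baseline and again at eight weeks |
| Primary and Secondary outcomes | Lists neither as an outcome |
| Statistical analysis, one-way ANOVA | Compares them between arms, at baseline only |
| Statistical analysis, paired t-test | Could describe change within an arm; compares no arms and adjusts nothing |
| Statistical analysis, main repeated measures ANOVA | Covers outcome variables, so not these |
| Statistical analysis, two-way repeated measures ANOVA (fourth objective) | Names no covariate |

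No ANCOVA, regression or other adjusted model is stated. The confounding claim therefore has no counterpart in the stated analysis.

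**Step 2. Separate the analyses at risk.** Arm comparisons are protected in expectation by randomisation. The association between vitamin D change and outcome change is not, least of all within an arm.

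**Step 3. Illustrate the size.** The documents give no correlations, so those below are assumptions. Let lifestyle change have the same correlation q with vitamin D change and with outcome change, and let vitamin D have no true effect.

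- Spurious correlation: r = q × q.
- Shift of the test statistic (Fisher z): m = arctanh(r) × √(n − 3).
- Two-sided rejection rate: Φ(m − c) + Φ(−m − c), with c = 1.960 at the 5% level and 2.576 at 1% (0.05/5, for the plan's five comparisons).
- n = 38 (one arm), 76 (two arms) and 152 (4 × 38), from the 38 per group in the Sample size section, before its attrition allowance.

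Worked case, q = 0.3 and n = 152: r = 0.09, m = 0.0902 × √149 = 1.10. The rate is 20% at the 5% level and 7% at the 1% level.

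| q | r | Level | n = 38 | n = 76 | n = 152 |
|---|---|---|---|---|---|
| 0.2 | 0.04 | 5% | 6% | 6% | 8% |
| 0.3 | 0.09 | 5% | 8% | 12% | 20% |
| 0.4 | 0.16 | 5% | 16% | 28% | 50% |
| 0.2 | 0.04 | 1% | 1% | 1% | 2% |
| 0.3 | 0.09 | 1% | 2% | 4% | 7% |
| 0.4 | 0.16 | 1% | 5% | 12% | 27% |

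**Step 4. Test the pooled figure.** With all arms pooled and no term for arm, half the women receive active vitamin D, so allocation drives part of the vitamin D change. If it explained half the variance (assumption), the first correlation would fall to 0.3 × √0.5 = 0.212. Then r = 0.212 × 0.3 = 0.064, m = 0.78, and the rates at n = 152 fall from 20% to 12% (5% level) and from 7% to 4% (1% level).

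The calculation uses a simple correlation test as a stand-in. It does not simulate the stated repeated measures ANOVA.

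**The case against.** The strongest reply is that this is silence in a condensed article. Covariates for a secondary association are often left to an analysis plan, and the sentence on confounding can be read as saying only that advice limits lifestyle drift and the questionnaires monitor it. Part of this stands: the article promises no statistical adjustment, does not link the sentence to the fourth objective, and nowhere says that the week-8 data will go unused. What remains is that the article does claim reduced confounding, ties its one named comparison to baseline, and states a model for the association without these terms.

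Three stronger readings are tempting, and the documents do not support them:

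- **The FBS result is confounded by lifestyle.** It is not: arms are randomised, and lifestyle change after randomisation may itself follow from treatment.
- **The trial cannot show whether the lifestyle instruction was kept.** Data from both visits in all four arms would allow this, and the paired t-test may already describe drift within arms. Only the between-arm comparison of change is not named.
- **The false-positive rate is materially inflated.** This rests wholly on assumed correlations, and the planned Bonferroni correction lowers the absolute rates.

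A further objection also stands. Adjusting for a change that runs alongside the outcome is not plainly better. Activity may change because mood or sleep changed, and adjustment could then distort the DASS-21 and PSQI associations.

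**Conclusion.** The point holds as a mismatch between a stated safeguard and the stated analysis, confined to one secondary, non-randomised objective. Following the article as written leaves the association between vitamin D change and outcome change unadjusted for lifestyle data already collected. No randomised comparison and no sample size figure changes.

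The mismatch itself needs no numbers. Its effect might range from negligible, at assumed correlations of 0.2 or less, to a clear excess of false associations at 0.4 in pooled data, and the documents cannot say where in that range the trial lies. Severity is minor.

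**What to change.** In Statistical analysis:

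1. Analyse the fourth objective by regressing outcome change on vitamin D change and arm. Report it both without and with the 8-week change in IPAQ MET-min/week and in energy intake. State that for DASS-21 and PSQI activity change may be a consequence of the outcome, so the adjusted result is a sensitivity analysis.
2. Replace the baseline test of diet and activity with a between-arm comparison of their 8-week change, as a check on the lifestyle instruction.
3. State that week-8 diet and activity will not be covariates in the randomised FBS comparisons, because they are measured after randomisation.

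In Strengths and limitation of study design, say that the questionnaires monitor lifestyle and support this adjusted secondary analysis.

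The cost is wording and a little analysis, with no new data, visits or participants. The downsides are a few degrees of freedom, the loss of women without week-8 forms from the adjusted model, and possible over-adjustment for mood and sleep. Reporting both versions makes that last risk visible.
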